### Study population, recruitment and eligibility criteria

Eligible participants will be recruited through our established trial-ready cohort (TRC) i.e., Hong Kong Cohort of Abnormal Sleep in Ageing Population (HK-ASAP) (ClinicalTrials.gov Identifier: NCT06170073) [26]. Potential participants will undergo screening by trained research assistants to assess eligibility and availability for this pilot trial. Both participants and their caregivers will receive a detailed briefing about this trial before providing informed consent.

Potential participants will need to satisfy the following inclusion criteria:

Chinese, right-handed, aged from 60 to 80 years.Sleep disturbances are defined as a Pittsburgh Sleep Quality Index (PSQI) total score above five [27].Subjective chronic tinnitus is defined as the tinnitus can only be heard by the patient, and there is no acoustic source [28]. The duration of chronic tinnitus is at least six months (as spontaneous recovery may occur among some patients in the first few months) [29].With no signs of cognitive impairments that are defined as a total score with the Montreal Cognitive Assessment (MoCA) above 26 (adjusted with educational level) [30].No interference with independence in everyday activities.

Exclusion criteria include:

Diagnosis of objective tinnitus is defined as the tinnitus produced by an internal acoustic source activating the cochlea and that can be heard by another person.Diseases of ear canal and tympanic membrane checked by otoscopic examination.Diagnosis of Meniere’s disease and acoustic neuromas.Past history of neurological or mental disorders.Physically frail affecting attendance to treatment sessions.Already attending regular treatments, such as cognitive behavioral therapy or music therapy.Taking a psychotropic or other medication known to affect hearing functions.Significant communicative impairments, such as severe hearing loss. The diagnosis of deaf or severe hearing loss will be informed by the medical records.

### Ethical issue

The pilot RCT will comply with the Declaration of Helsinki and the Good Clinical Practice guidelines of the International Conference on Harmonisation of technical requirements for registration of pharmaceuticals for human use (ICH-GCP). Ethical standards will be strictly adhered to this study, ensuring that written informed consent will be obtained from the participants and their anonymity, privacy, and confidentiality are respected. Participants will be able to withdraw from the study at any time, with no consequences and without giving any reason. This study has been approved by the Clinical Research Ethics Committee of The Chinese University of Hong Kong (CUHK) and New Territories East Cluster (NTEC) (The Joint CUHK-NTEC) (Date: January 24, 2023, Number: 2023.636) and was registered in the United States National Institute of Health Registration System with Clinical Trials (ClinicalTrials.gov Identifier: NCT06776705). All participant data, including audiometric results and health surveys, were anonymized at collection and stored on password-protected computers. Access was limited to study investigators, and data retention follows IRB guidelines (5 years post-study).

### Pre-treatment neuroimaging

#### Structural magnetic resonance imaging.

High-resolution structural magnetic resonance imaging (MRI) scans will be collected at the Prince of Wales Hospital using a 3.0 Tesla Siemens MAGNETOM Prisma MRI scanner (Siemens Healthcare Sector, Erlangen, Germany) equipped with a 32-channel head coil. T1-weighted magnetization prepared rapid gradient echo (MPRAGE) sequence is used to optimize the grey-white contrast, with following parameters [31]: repetition time (TR) = 2070 ms, echo time (TE) = 3.93 ms, axial acquisition with a 256 × 256 × 192 matrix, thickness = 1 mm, no gap, field of view (FOV) = 230 mm, flip angle = 15°. The sequence yields high quality isotropic images with the voxel size of 1 mm × 1 mm × 1 mm.

#### Diffusion magnetic resonance imaging.

To evaluate the glymphatic function, diffusion-weighted imaging (DWI) will be acquired in 30 independent directions along with five interleaved non-diffusion weighted (b = 0) images (1.9 mm3 resolution, TR = 8500 ms, TE = 81 ms, b = 700, echo spacing = 0.69 ms, GRAPPA iPAT factor = 2, 72 slices, 243 × 243 × 137 mm FOV). An accompanying phase map image is acquired using the same shim as the DWI sequence to correct for field inhomogeneities (4 mm^3^ resolution, TR = 1000 ms, TE = 3.60/6.06 ms, FA = 90°, 48 slices, 256 × 256 × 230 mm FOV).

### Randomization, allocation and masking

To ensure the homogeneous distribution between groups, all the eligible participants will be randomly assigned to receive either low-intensity TUS or sham TUS following a 1:1 ratio. A randomization assignment will be generated prior to study enrollment using an online system (http://randomization.com/) by a statistician who is not involved in the study design. After the randomization and baseline assessment, the participants will be scheduled for treatment sessions. Assessment staff and participants will be blinded to the study design and group allocation. The researcher who administers the TUS treatment will not participate in the assessments.

### Treatment strategies

#### Apparatus and settings.

NeuroFUS TPO and CTX-500-4 transducer (Brainbox Ltd., Cardiff, UK) are used in this clinical trial. This TUS system consists of a four-element ultrasound transducer (64 mm diameter) with a central frequency of 500 kHz [23]. We will use the theta-burst low-intensity TUS protocol with the following parameters [32]: pulse duration = 20 milliseconds, pulse repetition interval = 200 milliseconds and total duration = 80 seconds, giving a total of 400 pulses.

Based on individual’s structural MRI, we will construct head model of TUS and perform the transcranial acoustic simulations to ensure that we remain below the FDA guidelines for diagnostic ultrasound (MI ≤ 1.9; ISPPA ≤ 190 W/cm2) after transcranial transmission. We prepare each participant’s head by parting any hair over the intended target and applying ultrasound transmission gel (Aquasonic 100, Parker Laboratories Inc.).

### Stimulation modalities

#### Low-intensity transcranial ultrasound stimulation (TUS).

Theta-burst TUS (tbTUS) protocol will be used in this study for modulating neuronal activities and enhancing the neuroplasticity in hippocampal circuits [32,33]. The stimulation parameters of low-intensity TUS include Frequency: 5 Hz, pulse duration = 20 milliseconds, pulse repetition interval = 200 milliseconds and the total duration = 80 seconds, giving a total of 400 pulses.

#### Sham TUS.

For sham TUS (Placebo-controlled group), the transducer with ultrasound gel will be placed at the same location as active condition for 80 seconds with TPO power-off. This procedure mimics the skin sensation induced by ultrasound gel without producing any effects. To control auditory effects, we played a sound mimicking the pulse repetition and duration of low-intensity TUS.

### Grouping and treatment schedule

According to the design of this study, all the eligible participants will be randomly assigned to two groups: (1) Low-intensity TUS; (2) Sham TUS. After baseline assessment, the participants will start to receive a total of six successive sessions of low-intensity TUS treatment. This pilot trial is a 2-week treatment with three sessions per week, lasting for two weeks. Each session of treatment lasts for 80 seconds. The schedule for treatment is the same in the two randomized groups.

### Safety assessments

#### Adverse events checklist.

A checklist of adverse events associated with low-intensity TUS is applied to monitor tolerability and potential side effects. The Adverse Event Checklist (AEC) covering the symptoms from eight systems, including body as a whole, nervous system, cardiovascular, circulatory, digestive, musculoskeletal, urogenital systems and metabolic, is conducted at each assessment points through this pilot RCT [34].

### Outcome measures

#### Primary outcomes.

Subjective sleep quality: The Pittsburgh Sleep Quality Index (PSQI), as a 19-item self-report questionnaire, is used to evaluate the subjective sleep quality in a month [27,35]. The PSQI contains seven components. The subscore of each component ranges from 0 to 3, and the maximum total composite score of the PSQI is 21. The sum of these component scores yields a measure of global sleep quality. The cutoff score of poor sleep quality is 5 or more.Severity of tinnitus: Tinnitus functional index (TFI) is a 25-item self-administered questionnaire which assesses eight domains of tinnitus impact, including intrusiveness; sense of control; cognitive; sleep; auditory; relaxation; quality of life (QoL); emotion [36]. The TFI Chinese version (TFI-CH) has been validated for clinical and research purposes in Hong Kong [37].

#### Secondary outcomes.

Objective sleep quality: Actigraphic records were used to quantify sleep-wake cycle and estimate the objective sleep efficiency. The actigraph is about the size of a wristwatch and is usually worn on the wrist continuously for multiple days and nights, which can be used as an objective measurement of sleep quality and sleep-wake cycle in older adults.The Tinnitus Handicap Inventory (THI), as a reliable 25-item self-administered tool, is widely used in the studies of tinnitus treatment efficacy. The THI Chinese version (THI-CH) has been validated for clinical and research purposes in Hong Kong [38].Glymphatic function is assessed by the index of Diffusion Tensor Image Analysis ALong the Perivascular Space (DTI-ALPS) through DWI data [10]. DTI-ALPS is the quantification of the directional diffusion of water molecules with the perivascular space (PVS). The diffusivities in the directions of the x-axis (*D*_*x*_), y-axis (*D*_*y*_) and z-axis (*D*_*z*_) of the regions of interest (ROIs) on projection fibres and association fibres are recorded as *D*_*xproj*_*, D*_*yproj*_*, D*_*zproj*_*, D*_*xassoc*_*, D*_*yassoc*_*, D*_*zassoc*_, respectively [10,39].

### Assessment schedule

The comprehensive assessments, including sleep quality, severity of tinnitus, and adverse events, will be conducted at 1 week before low-intensity TUS treatment (baseline, T0), and at 2^nd^ week (T1), 6^th^ week (T2), and 12^th^ week (T3). Actigraphic records and Glymphatic function will be assessed at baseline and 2^nd^ week.

### Statistical analysis

The data analyst will be blinded to the randomization of participants. Analyses will be primarily conducted by the intention-to-treat (ITT) approach. The measurement scales for primary and secondary outcomes are continuous. Linear mixed effect models will be used to evaluate the differences between the conditions on primary and secondary outcomes measured at each time point. This statistical method will facilitate the inclusion of the participants with missing data. For handling missing data, multiple imputation will be used in this study. Treatment, time points, and their interaction will be modelled as fixed effects. Participants will be modelled as random effects at each time point. Pre-treatment subjective sleep quality, tinnitus symptoms, and cognitive performance will be compared between the two randomized groups. Score changes of sleep quality and tinnitus symptoms from baseline to follow-up points across randomized groups will be tested with occasions (time points) at level one and participants at level two. Covariates, including age, duration of tinnitus and PSQI total score, identified from baseline differences will be entered in the regression model. Secondary analyses of groupwise differences in the changes of glymphatic function, hearing function, and their associations between changes of tinnitus symptoms and sleep quality will be performed. We will also monitor the incidence of adverse events and the characteristics of program adherence. Statistical significance will be set at 2-sided *p* < 0.05. Computations will be performed using R Studio (version 1.1.456).

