## Materials and methods

### Research design

A two-arm RCT will be carried out with repeated measurements, including baseline, 2^nd^ week, 6^th^ week and 12^th^ week. It makes reference to the suggested requirements of a phase II design for non-pharmacological intervention. The study will be conducted following the Recommendations for Interventional Trials (SPIRIT) (Fig 1) and the Consolidated Standards of Reporting Trials (CONSORT) statement (http://www.consort-statement.org) (Fig 2).

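### Covariates are picked from chance baseline differences, so neither primary outcome is certain to be adjusted for its own baseline

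*Protocol article*

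**What the plan says.** All the relevant analysis text is in the Statistical analysis section of the protocol article.

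- Model terms: "Treatment, time points, and their interaction will be modelled as fixed effects".
- The effect is described in two ways. One is a between-arm difference at each visit: "Linear mixed effect models will be used to evaluate the differences between the conditions on primary and secondary outcomes measured at each time point". The other is a comparison of change: "Score changes of sleep quality and tinnitus symptoms from baseline to follow-up points across randomized groups will be tested".
- A baseline comparison comes first: "Pre-treatment subjective sleep quality, tinnitus symptoms, and cognitive performance will be compared between the two randomized groups".
- The covariate rule follows: "Covariates, including age, duration of tinnitus and PSQI total score, identified from baseline differences will be entered in the regression model".

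The Research design section counts baseline among the repeated measurements: "A two-arm RCT will be carried out with repeated measurements, including baseline, 2^nd^ week, 6^th^ week and 12^th^ week". The two primary outcomes are PSQI and TFI (Primary outcomes), and the Assessment schedule has sleep quality and tinnitus severity measured at baseline and at all three follow-up visits. PSQI total is therefore both a primary outcome and a named covariate. Baseline TFI is not among the three named covariates.

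**The concern.** The article states a rule here, so this is not a detail left to another document. Arms formed by randomisation differ at baseline only by chance. Letting those differences choose the covariates means that the model is settled after the data are seen. A covariate is then used because it happens to be imbalanced, not because it predicts the outcome. The best predictor of follow-up PSQI or TFI is likely to be the same score at baseline, and the rule guarantees neither.

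The role of baseline is also left open. It may be a response row, a covariate, or both, and the two descriptions of the effect lead to different estimators. This matters for a pilot whose stated purpose is to inform the effect size and sample size of a full-scale trial, because the estimate and its standard error depend on which estimator is used.

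**Working it through.** The plan gives no figure on this point to reproduce.

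**Inputs.** 15 per arm (30 in total, 1:1), effect 0.5 SD, two-sided 0.05: from the article. The correlation rho between baseline and follow-up is not in the article; 0.3, 0.5 and 0.7 are assumed. Outcome variance is set to 1 at each visit.

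**1. Reading A: baseline is a response row and the effect is treatment by time.** A covariate that is constant over time, entered as a main effect, shifts all of a participant's rows equally and cancels from any contrast against baseline. This was checked by fitting random-intercept models to simulated complete data (15 per arm, four visits). In one data set the week-2 contrast was 0.5755 (SE 0.340) both with and without baseline score and age, and equal to the raw difference in mean change. In the PSQI model, baseline PSQI would be both response and covariate, and as a covariate would do nothing to this contrast.

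**2. Reading B: change modelled at follow-up only, or the between-arm difference at a visit.** Here adjustment acts. In the same data set, with change as the response, entering baseline moved the week-2 effect from 0.576 to 0.257. For the between-arm difference at a visit in the four-row model with baseline as covariate, the variance factor at rho = 0.5 is 0.766, close to the 0.750 of analysis of covariance. Whether the covariate enters therefore decides the estimate.

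**3. Precision: change score against baseline adjustment.** The variance of the between-arm contrast is (2/n) times a factor: 2(1 − rho) for change and 1 − rho² for baseline adjustment. The ratio is 2/(1 + rho). Power is Φ(0.5/√(2 × factor/15) − 1.96), a normal approximation.

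| rho | Change factor | Adjusted factor | Change larger by | Power, change | Power, adjusted |
|---|---|---|---|---|---|
| 0.3 | 1.40 | 0.91 | 54% | 21% | 30% |
| 0.5 | 1.00 | 0.75 | 33% | 28% | 35% |
| 0.7 | 0.60 | 0.51 | 18% | 42% | 48% |

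These are large-sample values. Estimating the slope inflates the adjusted variance by 1 + 1/(2n − 4) = 1 + 1/26 = 1.038 at n = 15. The ratios become 1.538/1.038 = 1.48, 1.333/1.038 = 1.28 and 1.176/1.038 = 1.13, so the gain is slightly smaller but remains.

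**4. Effect of the selection rule where it acts.** The article gives no threshold for a baseline difference; p < 0.05 is assumed here. In 20,000 simulated trials per rho, the follow-up difference was adjusted for baseline only when the baseline test gave p < 0.05:

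| rho | SD, never adjusted | SD, by rule | SD, always adjusted | Type I error, by rule |
|---|---|---|---|---|
| 0.3 | 0.365 | 0.362 | 0.356 | 4.7% |
| 0.5 | 0.365 | 0.355 | 0.322 | 4.4% |
| 0.7 | 0.365 | 0.344 | 0.266 | 3.9% |

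At rho = 0.5 the rule keeps (0.365 − 0.355)/(0.365 − 0.322) = 0.010/0.043, about 23% of the gain in SD. Type I error lies below 5%.

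**5. Conditional bias.** Under the same assumed threshold, an imbalance must reach t(0.975, 28) × √(2/15) = 0.75 SD to trigger adjustment. An imbalance of at least 0.5 SD has a 17% chance per covariate: 2 × [1 − Φ(0.5/0.365)]. Given an imbalance of exactly 0.5 SD and rho = 0.5, an unadjusted follow-up difference shifts by rho × 0.5 = 0.25 SD, and a change-score difference shifts by (1 − rho) × 0.5 = 0.25 SD in the opposite direction. Each is half of the assumed effect of 0.5 SD.

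**The case against.** A reader might infer that the planned effect is definitely an unadjusted change-score difference that wastes the baseline data. The article does not support that. No sentence says that baseline is a response row or names the interaction as the effect, and one sentence points to differences at each visit instead. A change score also uses baseline, with slope 1. It removes the whole observed imbalance and, if anything, over-corrects.

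The two faults cannot both bite in the same analysis. If the effect is the interaction contrast, main-effect covariates are inert with complete data and choosing among them does no harm. If the choice matters, the effect is not the raw change difference. Exact inertness also needs complete data, and the article allows for 10% dropout.

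Further points stand. The selection uses baseline values and not outcomes, the analyst is blinded, and type I error is not inflated. Regression to the mean affects both randomised arms equally in expectation. The covariate list is introduced as non-exhaustive and baseline tinnitus symptoms are among the variables compared, so baseline TFI could enter under the rule. The double role applies to the PSQI model only. The trial is a declared pilot with acknowledged low power.

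These points limit the finding but do not remove it. A blinded analyst with coded arms still selects on between-arm differences, and a baseline that could enter is not one that will.

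**Conclusion.** The concern holds as a matter of precision and pre-specification, not of validity. The rule makes the primary model depend on chance imbalance and leaves adjustment of PSQI and TFI for their own baselines to luck. On one reading the named adjustment does not alter the effect; on the other, the rule decides whether the estimate is adjusted. Neither reading secures the gain that fixed baseline adjustment offers: against a change score, about 6 to 9 percentage points of power over the assumed correlations.

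The size rests on rho, which the article does not give, and on a normal approximation. The figures for the selection rule rest on an assumed p < 0.05 screen. The reading with baseline as a response is the most natural but is inferred. A claim of inflated false positives or a biased randomised comparison would go too far: the bias is conditional on an observed imbalance and averages out over randomisations. This should be fixed, as a free improvement, but it is not a must-fix defect.

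**What to change.** In the Statistical analysis section, delete the condition that covariates enter because of baseline differences, and state one treatment effect for each primary outcome. Then choose one of two models:

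- Use the post-baseline visits (weeks 2, 6 and 12) as responses, with treatment, time, treatment by time, and that outcome's own baseline as a pre-specified covariate: baseline PSQI for PSQI, baseline TFI for TFI.
- Or keep baseline as a response, with the arm means constrained equal at baseline, and do not enter the same baseline again as a covariate.

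Decide in advance whether age and tinnitus duration are included. They are optional, since each costs a degree of freedom with about 26 to 30 participants. Report baseline data descriptively, without using between-arm comparisons to choose the model.

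The cost is a change of wording, made before unblinding. The baseline scores are already scheduled, and no change to sample size, visits or data collection is needed.

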### Study timeline

The trial has been scheduled to take place from the 1st of January 2025 to the 1st of June 2026. By the end of February 2025, we successfully screened fourteen eligible participants who have completed MRI scanning.

## Discussion

This study presents the rationale and research protocol for a double-blind, sham-controlled pilot randomized clinical trial of using low-intensity transcranial ultrasound stimulation (TUS) to treat sleep disturbances in patients with chronic tinnitus. With the advantage of stimulating deep brain structures, low-intensity TUS has great potential for effectively modulating the activities of DMN, particularly hippocampus. Based on the hypothesis of targeting the “vicious cycle”, we expected that the patients who receive focused low-intensity TUS treatment will have more alleviations on sleep disturbances and tinnitus symptoms. It is also expected that the enhanced sleep quality and tinnitus symptoms will be related to better glymphatic function. This pilot trial stands out for a neuroscience-driven approach to address the non-pharmacological and non-invasive management of the comorbidities in older adults.

To our knowledge, this is the first randomized clinical trial evaluating the safety, feasibility and efficacy of focused low-intensity hippocampal TUS for treating sleep disturbances in chronic tinnitus patients. Adhering to the CONSORT checklist, this pilot RCT will employ rigorous methodology, including randomization by a blinded assessor and concealment of treatment differences from participants. Participants will be randomized by a blinded assessor and will not receive grouping information. Assessors and statistician will remain blinded to group allocation and have no contact with participants during the treatment period. The findings will provide high-level clinical evidence on the therapeutic potential of focused low-intensity hippocampal TUS for sleep disturbances in the clinical populations.

The findings of this pilot RCT will be circulated to international peer-reviewed journals, symposium and scientific conferences, regardless of whether the results are positive, negative or inconclusive in relation to the hypothesis.

